### Participant timeline {13}

Screening for infants meeting inclusion criteria is performed daily. The infant enrolled in the study will be randomized between 24 and 96 h after birth.

The first sample of blood is obtained soon after consent is obtained. The intervention will be stopped 28 days after birth; a second blood sample is collected with the next usual laboratory test after finishing the intervention (around 1 month postnatal), and the third sample at 36 weeks or before discharge, whichever occurs first.

The study intervention (placebo vs. extra vitamin D) is given if the infant is feeding within the first 28 days after birth and the vitamin D intake, relevant laboratory results, respiratory support, and growth parameters are obtained from the medical records during the NICU stay and during a 2-year follow-up appointment.

Standard follow-up assessments [26] will be conducted at 22–26 months’ adjusted age, including neurologic examination and neurodevelopmental and behavioral assessment. Additionally, we will collect data on long-term respiratory outcomes, including recurrent wheezing (modified International Study of Asthma and Allergies in Childhood questionnaire [27]) and respiratory infections, to evaluate early childhood pulmonary health (Fig. 1).

**Fig. 1 Fig1:**
[figure not shown]
Study schedule

### Sample size {14}

Assuming a mean 25-OH-D_3_ = 25 (standard deviation [SD] =12 ) ng/ml based on the data of a recent study [14] with a similar population and vitamin D supplementation to our routine care, 74 infants (37 in each group) affords ≥90% Bayesian power (with a >95% posterior probability) to identify an increase in serum 25-OH-D_3_ in the intervention group, assuming a true increase of 33%. We will assess the largest sample size feasible during the study period of 3 years (≥180 infants) to maximize precision in the estimate of effect and power for other outcomes based on our annual admission rate of infants that will qualify for the study, assuming a consent rate of 60%. Using a neutral Bayesian prior probability (RR = 1.0; 95% CrI, 0.3–3.3), 180 total patients afford 80% power to identify a >80% posterior probability (intervention arm) of reducing respiratory support (based on the described ordinal outcome) assuming a true RR decrease of 20% (RR = 0.80) and 90% power if the true RR decrease is 25%.

### Recruitment {15}

A dedicated and highly skilled research team is available 24 h per day, 7 days per week, to maximize recruitment, which is expected to end by July 2025.

## Assignment of interventions: allocation

### Sequence generation {16a}

The sequence is generated 1:1 with variable block size (4–6) using Research Electronic Data Capture (REDCap). Infants are stratified by BW (<750 g or ≥750 g) and assigned by enrollment order consecutively. Multiples are randomized separately.

### Concealment mechanism {16b}

The study statistician provided the allocation sequence to the investigational drug pharmacy (IDP), matching the assigned code with the intervention (placebo vs. vitamin D). After patient randomization, an encrypted email is sent by REDCap to IDP with name, medical record number, and assigned code.

### Implementation {16c}

The research team is notified when IDP receives the email to prepare the intervention, contact the medical and nursing team regarding the study’s first dose, and deliver support material to facilitate adherence to the protocol.

## Assignment of interventions: blinding

### Who will be blinded {17a}

Parents, clinical staff, and research personnel are blinded to the study arm. Only the statistician and IDP personnel know the allocation of the study patients. Our IDP ensures both arms’ quality control and regulatory compliance. Placebo and vitamin D (Enfamil Di-vi-sol® is a clear, odorless solution) have the same volume and appearance.

### Procedure for unblinding if needed {17b}

If there are concerns for vitamin D toxicity, the study drug or placebo will be stopped without unblinding the NICU staff and research team. The study statistician, NICU medical director, and the Institutional Review Board (IRB) will be notified of any infant considered to have signs suggestive of vitamin D toxicity and any infant with a serious adverse event by the National Institute of Health definition [28].

## Data collection and management

### Plans for assessment and collection of outcomes {18a}

The study data are largely obtained from the patients’ electronic medical record by the research team. Automatic data checks identify values outside the expected range at data entry to prompt verification that the data are correct.

Head circumference (assessed using tape) and length (assessed using a length board) are measured by research team members trained to achieve highly reliable measurements at 1 month and 36 weeks’ PMA.

Neurodevelopmental assessment, including BSID-IV at 22–26 months corrected age, Gross Motor Function Classification System, and hearing and vision evaluation, will be performed by certified examiners by the National Institute of Child Health and Human Development Neonatal Research Network [29]. Moderate or severe NDI is defined as a composite of neurologic, developmental, hearing, and vision status. Using the BSID-IV, a moderate delay in the cognitive domain is defined as 70–84, severe delay < 70, and profound delay ≤ 54. Other assessments include a Gross Motor Function Classification Score of ≥2, hearing impairment as bilateral permanent hearing loss that hinders the child’s ability to comprehend examiner directions, with or without amplification, and vision impairment characterized by bilateral acuity less than 20–200 with amplification.

Additionally, we will collect data on long-term respiratory outcomes, including recurrent wheezing (modified International Study of Asthma and Allergies in Childhood questionnaire [27]) and respiratory infections, to evaluate early childhood pulmonary health.

Vitamin D metabolite determination: A total maximum blood volume of <1 ml is obtained for the entire study duration (3 samples of 0.3 ml of whole blood), with daily clinical labs. Specimens are placed in a gold-top microtainer, stored in the research refrigerator until separation of serum in the next 6 h, and frozen at −80 F before shipping in batches for analysis to King’s University College in Ontario, Canada.

Vitamin D metabolites are extracted using liquid-liquid extraction (LLE) and immunoextraction [30, 31] and subjected to liquid chromatography-tandem mass spectrometry analysis using Waters ACQUITY UPLC/Xevo TQ-S instruments. The focus will be on abundant vitamin D metabolites, including 25-OH-D_3_, 25-OH-D_2_, and 3-epi-25-OH-D_3_.

### Plans to promote participant retention and complete follow-up {18b}

As in other trials in our NICU, we expect very few parents to want to withdraw their infant from the trial. If they do, we will stop the study drug and blood collection but ask the parents to allow us to include the infant’s clinical outcomes in our analyses. This approach, with a strong and innovative follow-up program with expertise in clinical trials with follow-up interventions [25, 32, 33], minimizes loss to follow-up and helps maximize the proportion of randomized infants included in our intention-to-treat analyses. Based on our experience with other studies, we expect to identify outcomes at 2 years for ≥80% of EP infants enrolled in this trial.

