### Additional consent provisions for collection and use of participant data and biological specimens {26b}

In the event of withdrawal from the study, the parents will be asked for their consent to continue the collection of electronic data. The consent form includes the collection of blood for vitamin D metabolites.

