### Relevant concomitant care permitted or prohibited during the trial {11d}

No more than 400 IU/day of vitamin D enteral supplementation as part of routine care is allowed in any group during the first 28 days after birth. The infant will only receive the study drug (extra vitamin D or placebo) if receiving feedings. The blood collection for enrolled infants is only collected with usual laboratory testing, and no additional venipuncture for the study will occur.

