### Outcomes {12}

The primary outcome is 25-(OH)D_3_ levels at 1 month after birth.

The secondary outcomes are indicators of likely or plausible effects of vitamin D supplementation on the function or structure of the lungs, bones, immune system, and brain, including:Respiratory support required at 36 weeks PMA using an ordinal scale (Table 2).Duration of respiratory support up to 2 years corrected age (CA), steroid treatment to decrease respiratory support, pulmonary hypertension at 36 weeks PMA, and wheezing at 2 years.Weight, length, and head circumference at birth, 1 month, 36 weeks’ PMA, and at 2 years’ CA. Fractures identified before NICU discharge and up to 2 years of CA. Serum calcium, phosphorus, and alkaline phosphatase levels during the first 28 days after birth and at 36 weeks’ PMA.Bayley™ Scales of Infant and Toddler Development, fourth edition (BSID-IV) neurodevelopmental assessments and NDI at 2 years’ CA.Hospital-acquired sepsis, length of stay, and readmissions.Serum concentrations of 25-OH-D_3_, 25-OH-D_2_, 3-epi-25-OH-D_3_, and 24,25-(OH)_2_D_3_ by liquid chromatography-tandem mass spectrometry.

**Table 2 Tab2:** Ordinal respiratory outcomes

**No BPD**	**Grade 1 BPD**	**Grade 2 BPD**	**Grade 3 BPD**	**Death**
No respiratory support	NC ≤ 2 L/min	NC > 2 L/min, non-invasive ventilation	Intubated mechanical ventilation	Death before 36 weeks PMA

*NC* nasal cannula

Severity graded according to the mode of support at 36 weeks PMA, irrespective of oxygen supplementation needs

Other outcomes are important differences between groups in other major clinical diagnoses are unexpected with our sample size and will be considered hypothesis-generating. We will report grade III–IV intraventricular hemorrhage, periventricular leukomalacia, surgically treated necrotizing enterocolitis, spontaneous intestinal perforation, stage III–V retinopathy of prematurity, and patent ductus arteriosus.

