### Methods in analysis to handle protocol non-adherence and any statistical methods to handle missing data {20c}

Per-protocol analyses will be conducted for the primary and major secondary outcomes using the same methods as for the interim analyses. The per-protocol analysis dataset will include all infants who received the randomized intervention (routine care or intervention).

If missing data occurs, it will be assumed to be noninformative (missing at random), and it will be imputed under a Bayesian framework by simulating from the posterior predictive distribution.

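### When parents withdraw an infant, blood sampling stops together with study drug, so an infant withdrawn before the 1-month sample has no measured primary outcome

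*Protocol article*

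**What the plan says.** Outcomes {12} makes the primary outcome the 25-OH-D3 "levels at 1 month after birth". Participant timeline {13} takes it from the second blood sample, drawn with the next usual laboratory test once the 28-day intervention has finished.

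On withdrawal, section {18b} first says "we expect very few parents to want to withdraw their infant from the trial". It then states the rule for those who do: "we will stop the study drug and blood collection but ask the parents to allow us to include the infant" in the analyses by way of clinical outcomes. It presents this approach, together with the follow-up program, as limiting loss to follow-up and helping to maximize intention-to-treat inclusion.

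Section {26b} says that on withdrawal "the parents will be asked for their consent to continue the collection of electronic data". Its next sentence, "The consent form includes the collection of blood for vitamin D metabolites", is not tied to withdrawal. Neither section describes asking withdrawing parents whether a further sample may be taken.

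The sample adds little burden. Section {11d} says "no additional venipuncture for the study will occur", and section {18a} describes three 0.3 ml samples taken with daily clinical labs.

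For missing data, section {20c} says "it will be assumed to be noninformative (missing at random") and imputed from the posterior predictive distribution.

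**The concern.** The withdrawal rule settles two questions at once: whether the infant goes on receiving study drug, and whether a small volume may be added to blood already being drawn. A family may answer these differently. As written, the second is not asked.

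The outcome affected is the primary one. Clinical outcomes can be read from the chart after withdrawal, so for those the approach serves its stated aim. A serum 25-OH-D3 level cannot. For an infant withdrawn in roughly the first month, the rule removes the one measurement that the primary intention-to-treat analysis needs.

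The imputed value may also lean one way. The models in {20a} contain treatment group, birth-weight stratum and a family effect. If the imputation uses the same terms, nothing in it reflects that study drug stopped. A withdrawn intervention infant would then be given about the level of infants who continued. If the true level is lower, the estimated difference between arms is too large. A control infant who stops placebo raises no comparable problem.

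**Working it through.** **Inputs.** From Sample size {14}: routine mean 25 ng/ml, SD 12, true increase 33%, at least 90% power at a posterior probability above 95%, 37 per group, at least 180 infants planned. From Trial design {8}: 1:1 allocation, so 90 per group. The documents give no withdrawal rate, so 2%, 5% and 10% are assumed.

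**1. The plan's own figure.** The assumed difference is 0.33 × 25 = 8.25 ng/ml. Reading the 95% posterior threshold under a near-flat prior as one-sided alpha 0.05:

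n per group = 2 × (1.645 + 1.282)² × 12² / 8.25² ≈ 36.2, rounded up to 37, or 74 in total.

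This matches the article. Power at 37 per group is 90.5% (90.0% with the noncentral t).

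**2. Power if 1-month samples are lost.** Same formula, starting from 180 infants:

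| Samples lost | Infants with a level | Power |
|---|---|---|
| 0% | 180 | 99.8% |
| 5% | 171 | 99.8% |
| 10% | 162 | 99.7% |
| 20% | 144 | 99.3% |

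The number falls to 74 only when 1 − 74/180 = 59% of samples are lost. Power is therefore not the issue.

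**3. Possible bias.** Let w be the share of intervention infants withdrawn before the sample, and r the fraction of the 8.25 ng/ml effect that they lose. If they are imputed at the full intervention mean, 25 + 8.25 = 33.25 ng/ml, then

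overstatement = w × r × 8.25.

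With r = 1, each such infant's true level is the routine mean of 25. The standard error of the difference at 90 per group is 12 × √(2/90) = 1.79.

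| w | Overstatement, r = 1 (ng/ml) | In standard errors |
|---|---|---|
| 2% | 0.02 × 8.25 = 0.17 | 0.09 |
| 5% | 0.05 × 8.25 = 0.41 | 0.23 |
| 10% | 0.10 × 8.25 = 0.83 | 0.46 |

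An infant withdrawn late in the 28 days has had much of the exposure, so r would be below 1. At r = 0.5 the figures halve, for example 0.10 × 0.5 × 8.25 = 0.41 at 10%. The table is an upper bound as long as withdrawn infants do not fall below the routine mean.

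**The case against.** Stopping research blood when parents withdraw is a defensible default, because the sampling rests on their consent. The article also condenses a fuller protocol and a consent form that are not shown, and a detailed menu of withdrawal options belongs there. Both points are fair. What remains is that {18b} states a rule, rather than leaving a gap, and that rule works against the aim given for it in the same section.

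The bias also rests on premises outside the documents. Section {20c} does not name the imputation model, no reason for withdrawal is given, and 10% fits poorly with an expectation of very few withdrawals. This stands, and it is why the size is given as a bound and the severity as low.

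A reader might infer more than the text supports:

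- **That parents who object only to study drug lose the sample.** The trigger is withdrawal from the trial. The article does not describe a drug-only objection.
- **That every withdrawal loses the primary outcome.** After the second sample the level is already in hand.
- **That sampling stops whenever drug stops.** Sections {11b} and {17b} stop drug for suspected toxicity, and {11b} also at the physician's discretion or while the infant is not fed. Neither stops sampling.
- **That the 2-year examinations are given up on withdrawal.** Section {26b} speaks of electronic data and {18b} of clinical outcomes, but {18a} says study data come largely from the electronic record, and {18b} does not exclude 2-year results. The wording differs; a contradiction is not shown.
- **That withdrawals are mostly for illness or poor tolerance.** The article does not say so.

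**Conclusion.** The point holds in a narrow form and is of low severity. Under the stated rule, an infant withdrawn before the 1-month sample has no measured primary outcome, although the sample could be had at almost no burden if the parents agreed. The cost is a few imputed values in the intention-to-treat analysis, with a possible lean toward the intervention of at most 0.17 ng/ml at 2% withdrawal and 0.83 ng/ml at 10%. That is about 0.1 to 0.5 of a standard error.

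The bound assumes early withdrawal, full loss of the effect, imputation at the full intervention mean, and withdrawal rates that the documents do not give. On the article's own expectation of very few withdrawals, the conclusion on the primary outcome is unlikely to change. The case for acting is that a measured value replaces an imputed one at little cost.

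**What to change.** In {18b} and {26b}, ask withdrawing parents, as a separate question, whether the 1-month sample and the 36-week sample may still be added to routine draws. Stop blood collection only if they decline. Use the same wording in both sections for continued use of records and of 2-year outcomes, so that it is clear what is being asked.

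No change is needed for infants whose study drug is stopped under {11b}, because no text stops their sampling.

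The cost is consent-form and protocol wording with IRB approval. It needs no extra venipuncture or sample volume. Under {25}, changes apply only to infants enrolled afterwards, so infants already in the trial would stay under the present rule.

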### Data management {19}

The data is entered and stored in a protected system (REDCap) with quality data checks (automated range checks for data values). Before performing the interim and final analyses, the statistician will perform quality checks and communicate with the research team if problems are encountered.

### Confidentiality {27}

REDCap is a secure online database, with minimal risk of loss of confidentiality. Personal identifiers will be removed from the information and samples collected in this study. A study number will be used to identify the patient for data analysis.

#### Plans for collection, laboratory evaluation, and storage of biological specimens for genetic or molecular analysis in this trial/future use {33}

The collected samples will be sent to [name] laboratory at King’s University College in Ontario, Canada, with the intent to analyze the vitamin D metabolites of the patients enrolled in the study. After a maximum of 3 years, they will be discarded.

## Statistical methods

### Statistical methods for primary and secondary outcomes {20a}

Intention-to-treat Bayesian analyses [21] will be performed using generalized linear mixed models for all outcomes. Covariates for the primary and secondary outcomes will include the treatment group and BW (<750 g, ≥750 g). All models will also include a random effect for family (to account for within-family correlation). The primary outcome of the 25-OH-D3 level will be analyzed with a linear mixed regression model, and the ordinal respiratory outcome will be analyzed with an ordinal logistic model. Binary outcomes will be analyzed with logistic regression, and data will be counted with a Poisson or negative binomial regression model. Priors will be centered at an odds ratio (RR for count data) of 1.0 (indicative of no difference between treatment groups with a 95% credible interval (CrI) of 0.3–3.3 and in the log OR scale a Normal distribution with a mean of 0 and variance of 0.70). A Normal(0, SD = 10) prior will be used for the intercept term, a Normal(0,1) for all other variables in the model, and half-Normal(0,1) for the SD of the random effect. We will report posterior medians and 95% CrI for group differences, ORs, RRs, and each outcome’s posterior probability of benefit.

All analyses will be conducted in R software latest version. Bayesian models will be fit using Markov chain Monte Carlo (MCMC) methods implemented in Stan via R packages “rstanarm” and “brms.” Each model will be fit using three MCMC chains. Each chain will have at least 5000 burn-in samples and at least 20,000 additional iterations. Convergence of MCMC chains will be assessed by visual comparisons of the trace plots for all parameters from the 3 chains generated for each model. Quantitative checks including the Geweke and Gelman/Rubin tests will be used to ensure convergence to the posterior distribution for all analyses.

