### Eligibility criteria {10}

Inclusion criteria: <28 weeks’ gestation (best obstetric estimate) or <1000 g BW; age <96 h at enrollment; inborn.

Exclusion criteria: GA ≥32 weeks; major anomaly; overt congenital nonbacterial infection; severe illness or immaturity that the attending neonatologist judges intensive care to be unjustified; or prenatal diagnosis of cystic fibrosis.

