### Methods for additional analyses (e.g., subgroup analyses) {20b}

Subgroup analyses of both RR/odds ratio and risk difference will be performed to assess effect modification by BW, gestational age, sex, race, infants who receive at least 80% of the possible doses (infants with minimal time when feedings were discontinued) and baseline 25-OH-D_3_ level (each assessed in one variable at a time analyses) and of different risk strata (assessed using multiple variables). Bayesian hierarchical models with interaction terms between the treatment group indicator and the prespecified potential modifiers will be used. The conservative Bayesian approach of Dixon and Simon [34] will be applied as it allows for a priori specification of how likely (or unlikely) it is for subgroup differences to be present, and to shrink the subgroup estimates to the overall mean treatment effect. The prior distributions for main effects will be the same for subgroup analyses as for the primary endpoint analysis. A Normal(0, SD = 0.7) will be used for interaction terms. Point estimates of treatment effect and 95% CrI for each subgroup will be reported along with probability of benefit using a forest plot.

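### The primary 25-OH-D3 model adjusts only for two-level birth weight and leaves out the baseline 25-OH-D3 value, giving up precision in a valid analysis

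*Protocol article*

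**What the plan says.** All references are to the protocol article.

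- **Adjustment set, {20a}.** "Covariates for the primary and secondary outcomes will include the treatment group and BW (<750 g, ≥750 g"). The only other term is for clustering: "All models will also include a random effect for family (to account for within-family correlation"). The primary analysis is a linear model: "The primary outcome of the 25-OH-D3 level will be analyzed with a linear mixed regression model". Coefficients of variables other than the intercept and treatment have a Normal(0,1) prior.
- **Baseline sample, {13}.** "The first sample of blood is obtained soon after consent is obtained". Section {11d} adds that blood is drawn only alongside usual laboratory tests.
- **Use of baseline 25-OH-D3, {20b}.** It appears only in the list of subgroup variables: "baseline 25-OH-D_3_ level (each assessed in one variable at a time analyses").
- **Gestational age.** It is known at entry, because eligibility {10} is "<28 weeks’ gestation (best obstetric estimate) or <1000 g BW". In the analysis it appears only under "effect modification by BW, gestational age, sex, race".
- **Sample size, {14}.** Control mean 25 and SD 12 ng/ml, a true increase of 33%, and 37 per group for at least 90% power with a posterior probability above 95%. At least 180 infants are to be enrolled, partly for precision. The objectives {7} name an increase of more than 33%.

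**The concern.** The primary outcome is a continuous blood level, and the same analyte is available from a sample taken near entry. In a linear model, an infant's own baseline is usually an obvious covariate: it removes between-infant variation and corrects chance imbalance between arms. The plan already treats baseline 25-OH-D3 as a baseline characteristic, since it is a subgroup variable, yet does not use it as a main effect.

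What is at stake is the width of the interval for the primary difference, and hence how firmly the trial can say that the increase exceeds 33%. The choice of 180 or more infants over the 74 needed for detection is justified partly by precision, so a cheap source of precision deserves use.

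Gestational age raises a lesser version of the question for the respiratory outcome. Section {22} notes high mortality in the most immature infants, and death is the worst category of the ordinal scale. Maturity enters that model only through the 750 g split.

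**Working it through.** **1. Reproduce the plan's figure.** From {14}: SD 12, difference 0.33 × 25 = 8.25 ng/ml. Treat a posterior probability above 95% as a one-sided 0.05 test with a flat treatment prior.

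n per arm = 2 × (1.645 + 1.282)² × (12 / 8.25)² = 36.2, rounded up to 37. Power at 37 per arm is 0.905. The stated 37 stands.

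**2. Power at the planned size.** At 90 per arm, SE = 12 × √(2/90) = 1.79 ng/ml. Power for any increase = Φ(8.25/1.789 − 1.645) = 0.998. Adjustment cannot improve this materially.

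**3. Gain from baseline adjustment.** SE = 12 × √(2/90) × √(1 − r²), and the equivalent unadjusted total is 180 / (1 − r²). Here r is the correlation of baseline with the 1-month level given birth weight. It is an assumption, and 12 is taken as the SD given birth weight. The family effect is ignored.

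| r | SE (ng/ml) | 95% half-width | Equivalent unadjusted N |
|---|---|---|---|
| 0 | 1.79 | 3.51 | 180 |
| 0.2 | 1.75 | 3.44 | 188 |
| 0.3 | 1.71 | 3.34 | 198 |
| 0.5 | 1.55 | 3.04 | 240 |
| 0.6 | 1.43 | 2.80 | 281 |

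**4. The objective of more than 33%.** Use the contrast (intervention mean) − 1.33 × (control mean). Suppose the true increase is 50%, which is an assumption. The contrast is then 37.5 − 33.25 = 4.25 ng/ml.

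- Unadjusted: SE = 12 × √((1 + 1.33²)/90) = 2.10; chance of a posterior probability above 95% = Φ(4.25/2.10 − 1.645), about 0.65.
- r = 0.5: SE = 2.10 × √0.75 = 1.82; chance about 0.75.

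**5. Whether the {20a} prior lets the covariate work.** Suppose the log of baseline is used with the outcome in ng/ml. Take r = 0.5 and a log-baseline SD of 0.5 (assumed).

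- True slope = 0.5 × 12 / 0.5 = 12 ng/ml per log unit, far outside a Normal(0,1) prior.
- Data precision on the slope is 180 × 0.5² / σ². With σ² near 128 this is about 0.35, against a prior precision of 1. The fraction of the slope retained is 0.35 / 1.35, about 0.26.
- Residual variance = 144 × 0.75 + (0.74 × 12 × 0.5)² = 108 + 19.7, about 128, which agrees with the value assumed.
- SE = √(128 × 2/90), about 1.69, against 1.55 with an unshrunk slope.

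Across log-baseline SDs of 0.4 to 0.6 the result is about 1.71 to 1.66. Most of the gain is lost unless the scale or the prior is changed.

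**6. Gestational age in the ordinal model.** This was checked with a proportional-odds simulation: 180 infants, 250 runs, conditional OR 0.65, prior SD ln(3.3)/1.96 = 0.61, and success at a posterior probability above 80%. The category rates and covariate strength were assumed. Two-level birth weight is compared with the same model plus a continuous maturity covariate:

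| Covariate strength | Power | SE of log OR |
|---|---|---|
| Weak | 0.75 to 0.74 | 0.270 to 0.273 |
| Moderate | 0.69 to 0.74 | 0.272 to 0.278 |
| Strong | 0.62 to 0.71 | 0.272 to 0.286 |

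Monte Carlo error of each power is about √(0.7 × 0.3 / 250) = 0.03. The SE rises slightly while the estimated effect moves away from zero, so any gain is in power.

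**The case against.** The strongest reply is that nothing here is an error. The model adjusts for the stratification factor and for family clustering, and it is unbiased. Primary power is ample, and the wording that covariates will include the listed terms leaves room for an analysis plan to add others. A longer covariate list may be only a reviewer's preference. Validity and power stand as stated. But section {20a} does name the adjustment set and leaves out the outcome's own baseline, and a possible addition elsewhere does not change that text.

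The size is also assumed. At r = 0.2 the gain is trivial (1.75 against 1.79). The relevant r is the one remaining after birth weight, and varied vitamin D intake during the month, about 160 to 600 IU/day in {6b}, adds variation that baseline cannot explain. This stands, and it is why a range is shown.

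A reader might infer that adjustment is free and available for every infant. The protocol article does not support that: blood is taken only with usual tests, and {13} does not say that the sample precedes the first study dose. Some baselines may be missing or post-treatment.

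A reader might also infer that leaving out gestational age biases the respiratory odds ratio or costs precision. It does neither. The odds ratio without it is a different, less conditional quantity, gestational age overlaps with birth weight, and the simulated gain is clear only for a strong covariate.

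Finally, enrolment began in September 2022 and the statistician knows the allocation ({17a}), so a change needs more than an edit. That stands and is met in the fix.

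**Conclusion.** The point holds as an efficiency weakness in the primary model. Leaving out baseline 25-OH-D3 keeps the SE of the difference at 1.79 ng/ml where it could be about 1.75 to 1.43 for r from 0.2 to 0.6. The practical benefit lies in interval width and in the objective of more than 33%, where the chance of success moves from about 0.65 to 0.75 if the true increase is 50% and r = 0.5. Both of those inputs are assumptions. The calculations also take an SD of 12 given birth weight, a flat treatment prior, no family clustering and complete pre-dose baselines.

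It would be wrong to conclude that the primary analysis is invalid, that 37 per group is miscalculated, or that detection of an increase is at risk. For the ordinal outcome, gestational age offers a modest gain in power that depends on how prognostic it is beyond birth weight.

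**What to change.** 1. Add continuous baseline 25-OH-D3 as a main effect in the primary model, keeping the birth-weight stratum and the family random effect.
2. Standardise outcome and covariate, or rescale the Normal(0,1) prior to the covariate's units, so that the slope is not shrunk away. If the outcome is standardised, restate the model's other priors on that scale.
3. Treat any baseline drawn after the first study dose as missing, and impute missing baselines under {20c}, so that no randomized infant is dropped.
4. As a secondary step, add continuous gestational age to the ordinal respiratory model, and state that the odds ratio is then conditional on it.
5. Record the change as a dated decision made blind to outcome data by arm. The interim analysis uses the final-analysis approach, so the change should cover both.

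The cost is imputation of some baselines and a documented mid-trial change to the analysis wording. No extra blood, visits or infants are needed.
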